## Methods

### Study aims

The aims of the OPEN AOS model evaluation are to:

Describe and compare the effectiveness and safety of the OPEN AOS model with standard ambulance attendance resulting in transport to ED care (standard care).Conduct an economic evaluation of the OPEN AOS model; and.Explore and understand the contextual factors influencing implementation to inform delivery and support potential scale and spread of the OPEN AOS model.

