## Setting

The study is set in the Metro North Hospital and Health Service (MNHHS) district in south-east Queensland, Australia [35]. In 2024, the MNHHS region had 87 RACFs (85 non-government) with 9417 RACF beds. The district is serviced by five public hospitals; four are classified as large or very large and one is classified as small. The EDs within each of the five hospitals vary in their level of service capability and capacity [36, 37].

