## Study design

This pragmatic multi-methods study comprises three discrete but related components: concurrent retrospective quantitative data collection for Components 1 and 2, and prospective qualitative data collection for Component 3. The approach to quantitative and qualitative data collection enables a comprehensive examination of the model’s effectiveness and real-world application. Given the multi-methods design, integration of quantitative and qualitative data through triangulation will not be undertaken. The design is underpinned by the integrated Practical, Robust, Implementation and Sustainability Model (PRISM) and Reach, Effectiveness, Adoption, Implementation and Maintenance (RE-AIM) framework [45]. PRISM will support the identification and description of contextual factors impacting RE-AIM outcomes [45]. This study has been reviewed and approved by the Metro North Human Research Ethics Committee (HREC) B (ECOO168), approval number 102,923. Data storage, retention and disposal will be conducted in accordance with the National Health and Medical Research Council (NHMRC) guidelines [46].

Three components are planned to address the following research questions:

*Component 1*

To what extent (if any) do patient characteristics (such as age, sex, and diagnostic classification^6^) and outcomes differ between OPEN AOS care and standard care (i.e. ambulance attendance with transport to ED care)?Specifically:

4.Primary Outcome: Time to be seen by treating clinician, defined as the amount of time in minutes from the initial contact with QAS to the time seen by either (i) the OPEN AOS clinician (intervention group) or (ii) the ED medical officer (control group).5.Secondary Outcomes:6.Length of care episode, defined as the amount of time in hours from initial contact with QAS to discharge of care.7.Ambulance transport to ED care: defined as the proportion of OPEN AOS patients requiring transport to ED for definitive care.8.ED re-presentation for any cause within 48 h and 28 days of discharge.9.Death within 48 h of discharge.10.Clinical incident^7^ [47] data, defined as clinical incidents that are reported by MNHHS staff that occur within 48 h of discharge.

*Component 2*

Compared to standard care, what is the incremental cost (saving) per person of the OPEN AOS model? 

*Component 3*

How do contextual factors influence implementation and potential future scale and spread of the OPEN AOS model?

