### Data collection and linkage

Patients living in RACFs are identified upon arrival to ED within EDIS^®^ and recorded as arriving by ambulance from a nursing home. Data extraction will occur retrospectively from state-based and MNHHS databases. An anonymous unique identifier (linkage ID) will be assigned to all cases by the Queensland Health Statistical Service Branch (SSB), enabling linkage of data from all sources (Table 1). These data provided to the researchers will not contain any key patient identifying features such as Unit Record Number (URN), name, address or Date of Birth (DOB). However, data such as age, postcode, and health facility will be included in the collection.

**Table 1 Tab1:** Data sources, date ranges and data descriptions for the OPEN AOS evaluation study

Data Source	Time Period	Data Description
RADAR Registry	1 Jul 2022 to 30 Jun 2023	OPEN AOS activity plus outcome data including: • outcomes of intervention • time stamps • clinician delegation Patient demographics for matching variables
Emergency Department Information System (EDIS^®^)	1 Jul 2022 to 28 Jul 2023	ED presentations of cohort members at one of the participating hospitals. • outcomes of intervention • time stamps Patient demographics and RACF address (presentation postcode and suburb) for matching variables
Metro North Health Funding and Data Insights	1 Jul 22 to 28 Jul 2023	Costs of initial ED presentations and subsequent re-presentations within 48 h and 28 days Patient unit record number for matching variables
Queensland Hospital Admitted Patient Data Collection	1 Jul 2020 to 30 Jun 2023	Patient co-morbidities identified during any hospital admission (using ICD-10-AM codes and ICD-10-AM code chapters), during the 24-month period preceding their presentations to the ED Patient demographics for matching variables
Death Registrations from the Registry of Births, Deaths and Marriages Queensland Cause of Death Unit Record File from the Australian Coordinating Registry	1 Jul 2022 to 02 Jul 2023	Death within 48 h of discharge from either emergency department presentation or OPEN AOS intervention Patient demographics for matching variables
RiskMan Queensland Health’s system for recording and managing clinical incidents, workplace events, consumer feedback, and risk	1 Jul 2022 to 02 Jul 2023	Patient Clinical Incident data within 48 h of discharge from the ED Patient demographics for matching variables

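### Clinical incidents are recorded by setting, and Table 1 ties the window to ED discharge only, so a between-group comparison may be biased by an unknown amount, probably towards OPEN AOS

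*Protocol article*

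**What the plan says.** All references are to the protocol article.

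- **Study aims.** The first aim reads "Describe and compare the effectiveness and safety of the OPEN AOS model with standard ambulance attendance", so safety is to be compared, not only described.
- **Study design, Component 1, outcome 10.** The incident outcome is "clinical incidents that are reported by MNHHS staff that occur within 48 h of discharge". It fixes who reports and when the incident must occur. It sets no time by which the report must be made.
- **Data collection and linkage, Table 1, RiskMan row.** The only incident source is RiskMan, "Queensland Health’s system for recording and managing clinical incidents, workplace events, consumer feedback, and risk". Its content is given as "Patient Clinical Incident data within 48 h of discharge from the ED".
- **Table 1, death row.** By contrast, this row reads "Death within 48 h of discharge from either emergency department presentation or OPEN AOS intervention".
- **Setting.** In 2024 "the MNHHS region had 87 RACFs (85 non-government) with 9417 RACF beds".
- **Component 1, Design and Data analysis.** Outcomes of the two groups will be compared. Models are named for the time outcomes, re-presentation and mortality, but none for incidents. Only the general sentence on Pearson chi-squared or Fisher tests for categorical data would reach them.
- **Limitations.** Selection bias, baseline differences and unmeasured confounding are listed. Unequal recording of incidents is not.

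**The concern.** An incident enters the analysis only if someone employed by MNHHS records it. Whether such a person is nearby in the 48 h after discharge depends on where the patient is. An OPEN AOS patient who stays in the RACF is mostly looked after by staff of a non-government provider. A control admitted from ED is on a ward among the named reporters, if the window runs from ED discharge. The chance of recording an incident can then differ between groups when the chance of harm does not. Matching on age, sex and diagnosis, and covariates in a regression, cannot restore an event that was never recorded.

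The wording of Table 1 adds a second problem. The RiskMan row does not name OPEN AOS discharge, so the data request may not cover the intervention group on the same terms as the control group.

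The stake is the safety conclusion for a model being considered for scale and spread: a low incident count under OPEN AOS could be read as reassurance when it partly reflects who was there to report.

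**Working it through.** **The plan's own figures.** 85/87 = 97.7% of RACFs are non-government. The only sample-size statement (351 and 1053, d = 0.2, two-sided 5%) reproduces at a power of 0.900. It concerns the primary outcome and is not in dispute. The article gives no rate, admission share or power for incidents.

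**Step 1: the two Table 1 rows side by side.** Death is anchored to discharge from ED or from OPEN AOS. Incidents are anchored to discharge from ED.
- Literal reading: an OPEN AOS patient who is never transported has no ED discharge and therefore no incident window.
- Generous reading: OPEN AOS discharge is meant as well. The window then exists in both groups, but the reporter and the source are still those of outcome 10.

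**Step 2: what unequal recording does under the generous reading.** All of the following inputs are assumptions, as the documents give none:
- a = share of controls in an MNHHS ward during the 48 h: 0 to 0.6
- s_W = chance that an incident on a ward is recorded: 0.8
- s_R = chance that an incident at the RACF is recorded by MNHHS staff: 0.1 to 0.3
- all OPEN AOS patients remain at the RACF

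Observed ratio (OPEN AOS/control) = true ratio × s_R / [a·s_W + (1 − a)·s_R].

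Example with a = 0.4, s_R = 0.1 and a true ratio of 1: 0.1 / (0.4 × 0.8 + 0.6 × 0.1) = 0.1/0.38 = 0.26.

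| a | True ratio 1, s_R = 0.1 | True ratio 1, s_R = 0.3 | True ratio 2, s_R = 0.1 | True ratio 2, s_R = 0.3 |
|---|---|---|---|---|
| 0 | 1.0 | 1.0 | 2.0 | 2.0 |
| 0.2 | 0.42 | 0.75 | 0.83 | 1.5 |
| 0.4 | 0.26 | 0.60 | 0.53 | 1.2 |
| 0.6 | 0.19 | 0.50 | 0.38 | 1.0 |

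A true ratio of 1 appears as 0.19 to 1.0. With some controls on a ward (a = 0.2 to 0.6), a true doubling appears as 0.38 to 1.5, so it could be hidden or reversed. If s_R were 0, the ratio would be 0 for any a above 0, so the lower end depends on the inputs chosen.

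**Step 3: let some OPEN AOS patients come under MNHHS care.** With share b, the numerator becomes b·s_W + (1 − b)·s_R. For b = 0.1, a = 0.4 and s_R = 0.1: (0.08 + 0.09)/0.38 = 0.45 instead of 0.26. The ratio is unbiased when a = b. The bias favours OPEN AOS when a exceeds b and incidents are recorded better on wards than at the RACF.

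**Step 4: how many events there would be.** At an assumed true risk of 2%, recorded incidents among 351 OPEN AOS patients would number 351 × 0.02 × 0.1 = 0.7 to 351 × 0.02 × 0.3 = 2.1. A test on such counts would say little even without bias.

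**The case against.** A reader might infer that the outcome is almost blind in the intervention group and that safety therefore cannot be compared at all. The documents do not support that, for these reasons:

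- **OPEN AOS clinicians can report.** The Component 3 participant criteria show that they are MNHHS employees. Outcome 10 dates the incident, not the report, so an RACF incident they learn of later still counts.
- **Some OPEN AOS patients return to view.** Those transported to or re-presenting at an MNHHS ED are again among MNHHS staff.
- **The gap is partly shared.** Controls are permanent RACF residents too, and those sent home from ED are no better observed. The asymmetry comes from controls still in MNHHS care, and no admission share is given. Nor does the article say whether a patient moved from ED to a ward counts as discharged at that moment. If the window starts only on return to the RACF, a is close to 0 and the bias largely disappears.
- **Other safety outcomes exist.** Death and ED re-presentation do not depend on incident reporting.
- **Details may lie elsewhere.** Additional file 2 and the footnote on clinical incidents are not shown.

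Each of these limits how large the bias can be said to be, and together they rule out a single headline figure. They do not remove the dependence on setting. The article describes no follow-up by OPEN AOS after discharge and lists no RACF incident source. They also leave the mismatch between the RiskMan and death rows untouched, and the one reading that removes the bias (a window starting on return to the RACF) is not the one that Table 1 states.

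**Conclusion.** The point holds in a limited form. The RiskMan row and outcome 10 do not give both groups the same stated window, and capture by MNHHS staff alone makes recording depend on where the patient is. Any resulting bias probably favours OPEN AOS, provided that more controls than OPEN AOS patients are in MNHHS care during the window and that incidents are recorded better there.

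Its size is unknown. The span of about 0.2 to 1.0 for a true ratio of 1 rests wholly on the assumed shares above, and its upper end is no bias at all. The finding does not reach the death or re-presentation outcomes, nor the primary outcome and its sample size. It should be corrected before incidents are compared between groups.

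**What to change.** 1. Reconcile the RiskMan row of Table 1 with outcome 10 so that both discharge points are named, as the death row already does, and say whether discharge for an admitted control means leaving the ED or leaving hospital.
2. Report incidents descriptively, by group and by place of the patient when the incident occurred (MNHHS care or RACF), with no between-group test.
3. State in the outcome definition and under Limitations that few reports after OPEN AOS discharge are not evidence of safety.
4. Base the comparative safety conclusion on linked death and ED re-presentation, noting that Table 1 limits ED records to participating hospitals in both arms.

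Death and ED records are already in Table 1. The cost is a wording change to one outcome, one table row and the limitations, and the loss of a between-group claim on incidents. If the RiskMan extract was specified on ED discharge alone, the request would also need to be widened to OPEN AOS discharge.

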### Component 1: Comparison of OPEN AOS model to standard care

#### Design

Component 1 is a retrospective, quasi-experimental design. This design was considered to be the most appropriate given the availability of pre-existing data and feasibility [48, 49]. Individual and treatment characteristics and outcomes for patients treated by OPEN AOS (intervention group) or received standard care (control group) will be compared. Figure 1 illustrates the potential patient pathways from the RACF, depicting management either by OPEN AOS or via ambulance attendance with transport to the emergency department (ED).

**Fig. 1 Fig1:**
[figure not shown]
OPEN AOS model patient journey following referral via emergency services

### Samples

In the 12-month study period from 1 July 2022 to 30 June 2023, approximately 7600 ED presentations from RACFs arrived by ambulance to district’s ED sites. During that same period, 735 patients were treated by OPEN AOS during their operational hours (08:00–20:00) Monday to Sunday. Patients treated in the Intervention group will be matched with up to three randomly selected control group patients without replacement with matching on age (+/- 5 years), and exact matching on sex and diagnostic classification section (or chapter if diagnoses are uncommon) as per the International Classification of Diseases, 10th Revision Australian Modification (ICD-10-AM) using the ‘R’ package Matching: Multivariate and Propensity Score Matching with Balance Optimization [50]. Groups sizes of 351 for the intervention group and 1053 for the control group will achieve 90% power to reject the null hypothesis of no effect on the time to be seen by treating clinician when there is a Cohen’s d small effect size of 0.2 using a two-sided, two-sample test assuming equal variance and an alpha of 5% [51].

### Inclusion criteria

Intervention: Adults aged 65 years or older who are permanent residents of RACFs situated within the MNHHS district geographical catchment area, with acute care needs and who were referred by the ambulance service to OPEN AOS between 08:00 and 20:00, Monday to Sunday, from 1 July 2022 to 30 June 2023. Patients can receive treatment by OPEN AOS on more than one occasion within the study period.

Control: Adults aged 65 years or older who are permanent residents of RACFs situated within the MNHHS district geographical catchment area, who received standard ambulance attendance and transport to a MNHHS ED between 08:00 and 20:00, Monday to Sunday, from 1 July 2022 to 30 June 2023. Only the first presentation for each patient within the study period will be examined.

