## Control: standard ambulance model of care

In Queensland, prehospital emergency care is provided by the Queensland Ambulance Service (QAS), a single, state-wide, government-funded emergency ambulance service. Like other Australian and international ambulance services, primary triage of calls is completed by a non-clinical Emergency Medical Dispatcher to determine the nature and type of incident, and the response time criticality. All incidents are assigned as either: emergency (potentially life threatening – immediate response with lights and siren); urgent (acute – immediate response with no lights and siren); or non-emergency (time critical scheduled conveyance or routine) response. Incidents are subsequently assigned either an immediate dispatch response or are transferred for clinical review performed by a multidisciplinary team of experienced paramedics, medical practitioners, mental health clinicians, social workers and Registered Nurses (RNs). Following clinical review, patients are assigned the most appropriate health response, which may include a dispatch response or referral to equivalent care pathway, and/or virtual care (i.e., health care consultation provided via telehealth platform run by RNs and medical practitioners). The majority of QAS patients (over one million annually) are transported from the scene [38], and approximately 90.0% of transports are to public hospital EDs [39].

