## Intervention: the OPEN AOS model

The OPEN AOS model provides emergency substitution care to older adults residing in RACFs located within the MNHHS catchment area. Nurse-led and physician supported, OPEN AOS commenced in January 2022 and became fully operational by June 2022. The service is based in office space adjacent to a MNHHS hospital and operates 12 h per day between the hours of 08:00–20:00, Monday to Sunday. The service aims to (i) decrease the time to treating emergency clinician and (ii) reduce the number of avoidable ambulance transports to ED for older adults living in RACFs. The OPEN AOS model is staffed by 3.0 full-time equivalent (FTE) Nurse Practitioners^1^ (NP); 1.0 FTE NP candidates (NPC)^2^; and 1.8 FTE RNs^3^ [40, 41]. The model is supported by 1.4 FTE Senior Medical Officers (SMO)^4^ [42, 43] and 0.8 FTE Senior Pharmacists 5 [44]. The service is funded by MNHHS. Detailed descriptions of the responsibilities of the OPEN AOS clinical roles are provided in Additional file 1.

Patients of OPEN AOS are older adults residing in RACFs experiencing acute illnesses or injuries. OPEN AOS clinicians provide emergency substitution care via telehealth or in person. Referrals originate from the ambulance service (either from paramedics attending the patient at the RACF or following secondary telephone triage by experienced ambulance service clinicians), General Practitioners (GPs), RACF staff and other local teams providing specialist sub-acute RACF consulting services. Each referral is reviewed by an OPEN AOS clinician who triages the case and determines suitability for OPEN AOS care. Patients not meeting eligibility criteria for the OPEN AOS remain in the care of ambulance services for secondary triage and receive standard clinical review, consideration of referral pathways and standard ambulance attendance.

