### Exclusion criteria

Patients were excluded if they (1) were assigned emergency status at primary (or secondary) triage (for any clinical reason); (2) did not reside in an RACF or resided in respite care; (3) were attended by ambulance and transported to ED care outside of OPEN AOS model operational hours (i.e. before 08:00 or after 20:00 Monday to Sunday); (4) were referred to OPEN AOS by any referrer other than ambulance services; or (5) received care outside the designated study period (1 July 2022 to 30 June 2023). (6) Patients included in the intervention group, i.e. those seen by OPEN AOS will be excluded from the control group.

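### Acute need is required only of OPEN AOS patients, so booked ambulance conveyances to ED can enter as controls and lengthen control times

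*Protocol article*

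**What the plan says.** All references are to the protocol article.

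- **Inclusion criteria, intervention.** Permanent residents aged 65 or over "with acute care needs and who were referred by the ambulance service to OPEN AOS between 08:00 and 20:00".
- **Inclusion criteria, control.** The same age and residence conditions, then those "who received standard ambulance attendance and transport to a MNHHS ED between 08:00 and 20:00". No acuity condition is attached.
- **Exclusion criteria.** The only exclusion based on priority is for patients who "were assigned emergency status at primary (or secondary) triage (for any clinical reason"). The other five concern residence, hours, referrer, study period and overlap with the intervention group.
- **Control: standard ambulance model of care.** QAS assigns one of three classes: emergency, urgent, "or non-emergency (time critical scheduled conveyance or routine) response".
- **Study design.** The primary outcome is "the amount of time in minutes from the initial contact with QAS to the time seen by either" the OPEN AOS clinician or the ED medical officer. Length of care episode starts at the same point.
- **Intervention: the OPEN AOS model.** "Each referral is reviewed by an OPEN AOS clinician who triages the case and determines suitability for OPEN AOS care". No matching screen is described for controls.
- **Samples.** Controls are selected by "matching on age (+/- 5 years), and exact matching on sex and diagnostic classification section", or by chapter when the diagnosis is uncommon.
- **Data analysis (Component 1).** The regression models adjust for triage score, weekend, season and ambulance referral time.

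**The concern.** The two inclusion sentences are nearly parallel, and the acuity condition stands in only one of them. Once the emergency class is excluded, the urgent and non-emergency classes remain, and the second of these includes scheduled conveyance. A resident booked in advance for ambulance transport to an MNHHS ED meets every printed control criterion. The corresponding non-acute case cannot enter the intervention group, because it fails the acute-need condition.

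The start of the clock is what makes this matter. If first contact with QAS is the booking, the planned interval before pick-up is counted as time waiting for a clinician. That would bias the primary outcome and length of care episode in a known direction, towards OPEN AOS, and shortening time to the treating clinician is one of the service's two stated aims. The study is powered for a small effect, so a small subgroup with long intervals could matter. The general caution about selection bias under Limitations does not deal with it, and this particular mismatch can be removed with data already requested.

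**Working it through.** **1. Can a booked conveyance enter each group under the printed criteria?**

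| Condition | Control | Intervention |
|---|---|---|
| Acute need stated | No | Yes |
| Clinician suitability screen | None described | Every referral |
| Emergency class excluded | Yes | Yes |
| Unscheduled non-emergency incident with acute need | Eligible | Eligible |
| Booked conveyance to ED without acute need | Eligible | Not eligible |

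The mismatch is confined to the last row.

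**2. Do the later steps remove it?** Matching uses age, sex and diagnosis section or chapter, none of which records whether transport was booked. Among the covariates, the article does not say whether triage score means ED triage or QAS priority, and none is stated to identify scheduled cases. These steps may remove some cases, but nothing shows that they remove them all.

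**3. The plan's own figure.** With 351 and 1053 patients, d = 0.2 and two-sided alpha of 5%: 0.2 / sqrt(1/351 + 1/1053) = 3.245, and Φ(3.245 − 1.96) = 0.901. The noncentral t gives 0.900. The stated 90% power reproduces and is not in dispute.

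**4. Possible size.** The documents give no share of booked cases (f), no booking-to-pick-up interval (L) and no SD (s) for time to clinician. All three are assumptions: f from 2% to 10%, L from 6 to 24 h, s from 120 to 180 min.

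- Planned effect in minutes = 0.2 × s: 24 min at s = 120, 36 min at s = 180.
- Shift in control mean = f × L: 0.02 × 360 = 7.2 min; 0.05 × 360 = 18 min; 0.05 × 720 = 36 min; 0.10 × 1440 = 144 min.
- The subgroup also inflates the control variance, by f(1 − f)L². At 5% and 12 h this is 0.05 × 0.95 × 720² = 24,624 min².

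Pooled SD at 5% and 12 h:

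- s = 120: sqrt[(350 × 14,400 + 1052 × 39,024) / 1402] = 181.3, so the standardised shift is 36 / 181.3 = 0.20.
- s = 180: sqrt[(350 × 32,400 + 1052 × 57,024) / 1402] = 225.6, so it is 36 / 225.6 = 0.16.

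Dividing 36 by s itself would give 0.20 to 0.30, which is too large because it ignores the inflated variance.

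The table gives the chance that the equal-variance two-sample test rejects when there is no true difference. Here SE = sqrt(s²/351 + control variance/1053), and the critical difference is 1.96 × pooled SD × sqrt(1/351 + 1/1053).

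| f, L | Shift | Standardised shift (s = 180 to 120) | False rejection (s = 180 to 120) |
|---|---|---|---|
| 2%, 6 h | 7 min | 0.04 to 0.06 | 9% to 14% |
| 5%, 6 h | 18 min | 0.09 to 0.13 | 32% to 57% |
| 5%, 12 h | 36 min | 0.16 to 0.20 | 77% to 95% |

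**5. If the rank test is used.** The plan allows Mann-Whitney. In the worst case every booked control waits longer than every intervention patient, so P(control > intervention) = 0.5 + f/2, which is 0.525 at f = 5%. The null SE is sqrt[1405 / (12 × 351 × 1053)] = 0.0178, so z = 0.025 / 0.0178 = 1.40 and the false rejection rate is at most about 29%. At f = 2%, z = 0.56 and the rate is about 9%. The length of the delay then no longer matters, only the share.

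**The case against.** The strongest reply is that the criteria show what could happen, not what did. The list of QAS classes covers all incidents, and no section says that booked conveyances from RACFs go to an ED. Controls are recorded on the ED system as arriving by ambulance from a nursing home, and their outcome is time to an ED medical officer. Attending an ED is itself a fair proxy for acute need. Exact matching on diagnosis section also bars any planned attendance whose diagnosis has no intervention counterpart. The share, delay and SD above are all assumed. The article is condensed, and a fuller protocol may hold the dispatch-code filters. Most of this stands as to size. It does not remove the asymmetry, because both criteria are printed and only one carries the condition.

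A reader might infer more than the documents support, in four ways:

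- **That all routine non-emergency responses are part of the problem.** The control section lists routine and scheduled conveyance as alternatives. A routine response need not be booked, so a planned delay cannot be assumed for it.
- **That the intervention group has no non-emergency cases.** Nothing bars a non-emergency incident with acute need from OPEN AOS. Only non-acute booked trips lack a counterpart.
- **That matching and adjustment cannot help.** They may remove part of the effect; they are just not shown to remove it.
- **That this subgroup produces the planned effect.** It does so only with shares and delays from the middle of the assumed range upward. At 2% and 6 h the shift is 7 min against a planned 24 to 36 min.

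**Conclusion.** The point holds in a narrow form. As printed, the eligibility rules admit booked ambulance conveyances to an MNHHS ED as controls while requiring acute need of intervention patients. If such cases occur, and if first contact with QAS is taken as the booking, the planned interval lengthens control times for the primary outcome and length of care episode and favours OPEN AOS. The direction is predictable. The size is unknown and may be small: under the assumed ranges it runs from a standardised shift of about 0.04 (2%, 6 h, SD 180 min) to about 0.20, the whole planned effect (5%, 12 h, SD 120 min), and further if both share and delay are larger. These figures describe unadjusted comparisons of means; a rank test would be less sensitive. The sample size calculation is unaffected. The change is worth making because it is specific and cheap and can be made before analysis.

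**What to change.** 1. State the acute-need condition in the inclusion criteria of both groups.
2. Put it into practice with the QAS dispatch-response data already listed in Table 1: exclude only scheduled or pre-booked conveyances, from both groups. Keep unscheduled urgent and unscheduled non-emergency incidents. Dropping all routine responses could remove low-acuity unscheduled cases typical of OPEN AOS and create a new imbalance.
3. Report the number removed from each group. This also settles how large the problem was.
4. Add a sensitivity analysis of the primary outcome and length of care episode that adjusts for, or restricts by, QAS response class.

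The cost is one added clause, one filter on data already requested, and a slightly smaller control pool. With about 7600 ambulance presentations from RACFs before exclusions, against 1053 controls in the power calculation, the loss should be affordable. Because the data are retrospective, neither recruitment nor patient care changes.
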